### HTA-supported medical decision making in MSA

In parallel to the clinical study, we aim to develop decision-analytic models for evaluating MSA test and treatment strategies. We will create a model framework and conduct a literature search to inform decision-analytic models, which simulate MSA disease progression, diagnostic work-up, different treatment pathway, health states and events (Roberts et al. 2012; Siebert et al. 2012). The model parameters will be informed by QoL data from the historical EMSA-SG, the MeDeMSA Care cohort and substantiated by a literature search. The decision-analytic model design, analyses and reporting will follow the international methods guidelines of the ISPOR-SMDM Modeling Good Research Practices Task Force, (Caro et al. 2012), key principles of health technology assessment (HTA) and the CHEERS 2022 reporting guidelines for economic evaluations (Drummond et al. 2008; Husereau et al. 2022). Our model will evaluate test-treatment strategies across the remaining lifetime of recruited individuals with MSA, assessing benefits (e.g., increase in life expectancy, quality-adjusted life expectancy), harms (e.g., complications, adverse events), and costs (e.g., diagnostic procedures, treatment, travels), and trade-offs such as harm-benefit and cost-effectiveness ratios. The evaluation will include both a healthcare system perspective and a societal perspective.

## Trial time plan and regulatory aspects

The MeDeMSA Care study commenced in April 2023 and is planned to last five years, with an expected active recruitment phase of 27 months. Following a six months preparatory phase, the MeDeMSA Care Study protocol was approved by the Ethical Committee of the Medical University of Innsbruck (EK No.: 1225/2023) and Medical Director of the Tirol Kliniken in September 2023, and started recruiting in October 2023. The study adheres to the principles of the Declaration of Helsinki, the current European Data Protection Regulation, and the Austrian Agency for Scientific Integrity. Monitoring visits will be carried out by the Innsbruck Competence Center for Clinical Studies in due course.

By the time of the manuscript revision (March 2025), 23 individuals with MSA and 20 informal MSA caregivers have been actively recruited. Regular MeDeMSA Care trial status updates are released on ClinicalTrials.gov (NCT06072105).

## Discussion

At early disease stages, individuals with MSA are usually able to attend specialized clinics, where healthcare provision focuses on symptom control and maintaining autonomy in daily life. At advanced stages, healthcare goals shift towards maximizing the QoL and preventing medical complications. However, by the wheelchair-bound stage, physical and organizational barriers often prevent access to specialized MSA care. Physicians frequently lose track of individuals with advanced MSA, who face life-threatening complications and receive limited support. Beyond mobility and communication problems, the loss of “connection to others” was indeed found to most heavily impact QoL in people with advanced parkinsonism (Strupp et al. 2018; Wiblin et al. 2017). Palliative care plays a crucial role in addressing the physical, psychosocial, and spiritual needs of individuals with life-limiting illnesses (Jasemi et al. 2017). Tailored to cultural and educational backgrounds, it involves mobile teams, hospices, and family caregivers in a holistic approach to care (Breitegger et al. 2024). A key component is advance care planning, which enables individuals to express their healthcare preferences and make healthcare decisions in anticipation of a time when they may no longer be able to express their preferences (Breitegger et al. 2024). Studies however showed that, for individuals with MSA with do-not-resuscitate orders, discussions on advance healthcare directives often occurred only few hours before death (Dayal et al. 2017), highlighting major unmet needs for tailored healthcare strategies throughout the disease course.

We hypothesize that, while efforts are underway worldwide to develop effective disease-modifying strategies, establishing protocols for multidisciplinary, patient-centered symptomatic care may influence the course of MSA by improving the QoL of affected individuals (Bloem et al. 2020) and potentially reducing the occurrence of life-threatening medical complications. Various studies across Europe and the US are exploring different support approaches, including tailored counselling (NCT04965922), educational programs (NCT05819957), assessments of multidisciplinary care impact (NCT03811808), healthcare service utilization (NCT06645626), and remote integrated care to improve monitoring and reduce hospital visits (NCT05792332). MeDeMSA Care is the first study integrating in-person multidisciplinary visits with mobile palliative care, medical, psychological, and neurorehabilitation counselling via telemedicine for individuals with MSA. In this context, mobile palliative care teams may help to overcome the physical barriers between people with MSA and their specialists, particularly towards the end of life. Even though telemedicine in MSA remained underexplored so far, digital health technologies likewise offer potential for cost-effective, high-quality care delivered throughout the disease course (Pinto et al. 2017). Additional measures are likely required for a safe telerehabilitation practice. For this purpose, the MeDeMSA Care neurorehabilitation interventions have been designed in a modular format with varying levels of difficulty (see Supplementary Materials 2, 3 and 4), enabling personalized recommendations based on the level of disability and neurorehabilitation needs identified during in-person assessments. Satisfaction surveys will ultimately help to identify barriers and strategies to improve this novel treatment format. Psychological counselling over telemedicine can additionally provide support to individuals living with MSA and their caregivers in coping with fears and concerns. Despite the high symptomatic burden of MSA, caregiver burden remains in fact poorly understood and should be factored into health-economic studies (Chan et al. 2023). We hypothesize that a multidisciplinary approach, including mobile palliative care and telemedicine, could improve disease management and consequently reduce caregiver burden, particularly in advanced stages.

In clinical practice, access to multidisciplinary care is often limited by the scarcity of specialized services outside MSA referral centers (Coon et al. 2022; Reis-Carneiro et al. 2024) and the uneven distribution of care providers across countries (Habek et al. 2022). Centralized care models contribute to such disparity, as individuals residing farther from MSA referral centers often receive suboptimal care and remain underrepresented in clinical studies (Campese et al. 2024). Beyond the trial horizon and the abovementioned strategies to abate physical barriers, the MeDeMSA Care study aims to bridge this gap in healthcare access by developing test-treatment algorithms, which include widely available diagnostic tools and easily accessible, scalable, therapeutic options, including neuro-rehabilitation. Such algorithms are made available to the readership in the supplementary material of the present manuscript (see Supplementary Materials 1, 2, 3, 4) and may assist neurologists outside referral centers in delivering multidisciplinary MSA care.

## Potential study limitations

MeDeMSA Care's monocentric design and MSA’s rapid progression pose recruitment and retention challenges, with risks of dropout due to treatment noncompliance or fatal events. Recruitment empowering strategies are therefore regularly implemented. The re-assessment of the patient’s health-care goals at month-12 should also minimize the risk of incompliance. In case the drop-out rate will exceed current estimations, recruitment may be extended to achieve the targeted population size. To ensure continuity of care, individuals not randomized to the telemedicine arm may replace in-person follow-ups with telemedicine visits if disease progression prevents travel. While this safeguards ongoing care to the individuals participating in the MeDeMSA Care study, it may introduce a retention bias, favoring more severe cases that would have likely been lost to follow-up in the EMSA-SG study.

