## Methods

### Study design

This 18-month, monocentric, open-label study evaluates the impact of multidisciplinary, personalized best medical care, including mobile palliative and telemedicine support on the EQ-5D-5L score change of prospectively recruited MSA individuals compared to a sex-, age- and disease-duration matched historical European MSA cohort that received standard care [EMSA-SG cohort, (Wenning et al. 2013)], and whose data is stored at the Medical University of Innsbruck. The EMSA-SG cohort included individuals with MSA from ten countries, who underwent in-person assessments every six months over a 24-month period, showed largely comparable clinical-demographic characteristics across countries, but did not regularly receive treatment for MSA non-motor symptoms, neurorehabilitation, psychological counselling or palliative care offer (Kollensperger et al. 2010).

The study also assesses the participants'motor progression over 18 months using the Unified MSA Rating Scale (UMSARS) Part II through blinded video evaluations. Their progression is then compared to the motor progression curves of matched individuals from the EMSA-SG cohort.

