**Table 2 Tab2:**
[figure not shown]
MeDeMSA Care Patient Visit Plan

During follow-up in-person visits at 6-, 12-, and 18-months, the therapeutic needs are reassessed and the treatment plan is adapted as required. If subjects cannot travel to the center, they are offered the possibility to complete the scheduled on-site assessments via the CHES online platform. At month-12, the semi-structured interview is repeated to evaluate changes in healthcare preferences due to disease progression. Follow-up calls are scheduled one month after each in-person visit (at months 1, 7, and 13) to verify treatment compliance and address barriers. Short Assessment of Patient Satisfaction (SAPS) surveys are administered online at months 1, 7, 13, and 18 to evaluate the overall individual satisfaction with the treatment plan. In case additional in-person visits are scheduled, the reason for such visits and eventual therapeutic adaptations are documented.

Upon completion of the baseline assessment, 23 patients are block-wise randomized to additionally receive monthly and on-demand telemedicine visits for neurological, psychological, and neurorehabilitation support via CHES. If the individuals randomized to receive additional telemedicine visits own a tablet or computer with a ≥ 10-inch display, they may use it to enhance digital comfort. Otherwise, a CE-certified tablet (e.g., SAMSUNG Tab A7 T505 LTE 32 GB) is provided. The MeDeMSA Care team members are asked to rate telemedicine feasibility and potential barriers beforehand. After each telemedicine visit, healthcare providers give feedback on how the visit was conducted, document any challenges encountered, and note the adopted strategies to solve them. Brief patient satisfaction surveys follow telemedicine and mobile palliative care interventions: these include a 0–10 rating scale for the overall satisfaction with the intervention and open-ended questions about its advantages and disadvantages. The MeDeMSA Care team holds regular meetings every six to eight weeks to review changes in the care needs of recruited individuals with MSA and coordinate additional support as required.

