## Statistics

### Sample size calculation

The sample size for the present study has been estimated based on data of the EMSA-SG natural history study (Wenning et al. 2013). In this historical cohort, individuals with MSA showed an average EQ-5D score at baseline of 0.35 (95% CI 0.27–0.42), which worsened to 0.17 (95% CI 0.06–0.28) over an observational period of 18 months under standard care (Wenning et al. 2013). In other chronic medical conditions, treatment is considered to be positively associated with QoL, if the EQ-5D score change in the interventional group averages 0.08 points above that of the control group at follow-up (Kwakkenbos et al. 2013). If effective, we therefore estimate the MeDeMSA Care program to limit the baseline to 18 months EQ-5D worsening to 0.25 (± 0.25 standard deviation, SD) in the MSA individuals receiving personalized best medical care with integrated mobile palliative and telemedicine support, as needed. With an assumed significance level of 5% and a power of 80%, 46 individuals with MSA should therefore enroll in the trial to observe an effect of the personalized multidisciplinary care program compared to the standard care offered to the historical MSA cohort, including an expected drop-out rate of 10% over the study course.

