### Data analysis

The distribution of quantitative data will be assessed using the Shapiro–Wilk test. Quantitative variables will be reported as mean (± SD) for normally distributed data or median (interquartile range, IQR) for non-normally distributed data, and qualitative variables as counts (percentages). Qualitative variables will be compared using Pearson’s Χ^2^ test (or Fisher’s exact test, if n < 5) and quantitative variables using the Mann–Whitney U or t-test, depending on the data distribution. A Benjamini–Hochberg correction will be applied for multiple tests, whenever appropriate. Binary logistic regression with a receiver operating characteristics (ROC) area under the curve (AUC) calculation will follow univariate analysis when applicable.

Changes in EQ-5D, motor, and non-motor scores between the MeDeMSA Care cohort and age-, sex-, and disease duration-matched historical EMSA-SG individuals will be evaluated with ANOVA for repeated measurements or linear mixed models, as most appropriate. Comparisons between randomization groups and the historical cohort will be run on a descriptive basis, with post-hoc tests adjusting for type-1 error based on ANOVA results.

QoL and caregiver burden changes in caregivers of MSA individuals receiving personalized best medical care with or without telemedicine will be analysed with ANOVA or linear mixed models, adjusted for the disease stage of the cared-for individual with MSA. Correlation analyses will assess the relationship between the caregivers’ QoL and burden with the disease characteristics (e.g., symptom constellation and severity) of the cared-for individual with MSA.

Statistical analysis will be performed with SPSS version 30.0.0 or future releases. P values below 0.05 will be considered statistically significant, with 95% confidence intervals considered where appropriate.

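### Patients who can no longer travel can stay in the new cohort's EQ-5D data but probably not in EMSA-SG's; the article concedes this, yet its primary analysis is not adapted to it, which may bias the 18-month comparison

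*Protocol article*

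**What the plan says.** The primary comparison sets the 18-month EQ-5D change of the new cohort against matched EMSA-SG patients.

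- **Observation in EMSA-SG** (Protocol article, Study design): patients "who underwent in-person assessments every six months over a 24-month period".
- **Observation in the new cohort** (text after Table 2): "If subjects cannot travel to the center, they are offered the possibility to complete the scheduled on-site assessments via the CHES online platform". The Fig. 1 footnote says the same for months 6, 12 and 18, for any legitimate reason. Potential study limitations extends remote replacement to participants outside the telemedicine arm when progression prevents travel.
- **The concession** (Potential study limitations): "it may introduce a retention bias, favoring more severe cases that would have likely been lost to follow-up in the EMSA-SG study".
- **The analysis** (Data analysis): EQ-5D changes in the two cohorts "will be evaluated with ANOVA for repeated measurements or linear mixed models, as most appropriate". The article connects no rule on which records enter the model, and no sensitivity analysis, to the retention difference.
- **The target** (Sample size calculation): success is an "EQ-5D score change in the interventional group averages 0.08 points above that of the control group at follow-up".

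**The concern.** The two sides of the primary comparison follow different observation rules, and the difference bears on the sickest patients. If those patients leave the historical data but stay in the new data, low late EQ-5D values enter mainly on the programme side. The historical decline then looks milder than it was, and a real benefit shrinks.

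A mixed model handles loss that earlier recorded scores explain. It does not handle loss that depends on deterioration since the last visit. Visits are six months apart and the stated trigger for remote completion is progression that prevents travel, so that second kind of loss is plausible. The countermeasures in Potential study limitations (recruitment strategies, goal reassessment at month 12, longer recruitment) do not act on this difference between cohorts.

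**Working it through.** **Target.** EMSA-SG had an "average EQ-5D score at baseline of 0.35 (95% CI 0.27–0.42), which worsened to 0.17 (95% CI 0.06–0.28". The programme is expected to "limit the baseline to 18 months EQ-5D worsening to 0.25", which the arithmetic shows to be a level at 18 months: 0.25 − 0.17 = 0.08. The article gives no figure for the retention difference, so its size can only be shown over a range.

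**Inputs.**
- From the article: means 0.35 at baseline and 0.17 at month 18; SD 0.25.
- Assumed: linear course between (0.29 and 0.23 at months 6 and 12); between-visit correlation ρ = 0.6; share p unable to travel by month 18 of 15, 25 or 35%; those unable to travel score d = 0.18 to 0.29 lower than the rest at month 18; every such patient lost from EMSA-SG and none from the new cohort.

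**Hand approximation, no true effect, loss driven by the current score.** The mixed model recovers the part of the gap that the three earlier visits predict:

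R² = 3ρ² / (1 + 2ρ) = 3 × 0.36 / 2.2 = 0.49

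bias ≈ −p × d × (1 − R²)

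| p | p × d | × 0.51 | simulated mixed-model bias |
|---|---|---|---|
| 15% | 0.027 to 0.044 | 0.014 to 0.022 | −0.011 to −0.021 |
| 25% | 0.045 to 0.073 | 0.023 to 0.037 | −0.022 to −0.037 |
| 35% | 0.063 to 0.102 | 0.032 to 0.052 | −0.032 to −0.051 |

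The last column is a simulation of 60,000 patients per cohort under these inputs, analysed by maximum likelihood. As a share of the target, 0.011/0.08 = 14% and 0.051/0.08 = 64%.

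**The same set-up with other loss mechanisms.**
- Loss split equally between the last observed and the current score: −0.007 to −0.031.
- Loss dependent only on the last observed score: about 0 (−0.003 to 0.001).

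**A second simulation with a true difference of 0.08**, SD of change about 0.27, and assumed drop-out in EMSA-SG/new cohort of 20%/0, 30%/10%, 40%/10% and 40%/0:

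| Loss depends on | complete cases | mixed model |
|---|---|---|
| nothing | 0.08 | 0.08 |
| last observed score | 0.066 to 0.073 | 0.080 to 0.081 |
| last and current score | 0.037 to 0.060 | 0.031 to 0.057 |
| current score | 0.013 to 0.048 | −0.002 to 0.040 |

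The complete-case column stands for a repeated-measures ANOVA restricted to patients with all visits. It is biased even where the mixed model is not.

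**Does the remedy work?** With the in-person rule applied to both cohorts and loss driven by the current score, the null bias is −0.002 to 0.002. With a true 0.08, the all-data model gives 0.030 to 0.068 and the like-for-like model 0.068 to 0.078.

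**Indirect evidence on EMSA-SG loss.** The half-width of the 95% interval rises from (0.42 − 0.27)/2 = 0.075 to (0.28 − 0.06)/2 = 0.11. At constant SD, the share still measured at month 18 would be (0.075/0.11)² = 46%. A larger SD at month 18 would widen the interval equally, so this is compatible with attrition but does not show it.

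**The case against.** **The authors already disclose it, and a full protocol or SAP may handle it.** Both are fair. Missing-data sensitivity analyses are often left to documents not shown here, and the absence of one is not the point. What stands is that the article states a bias in its own primary comparison and names a primary model that does not deal with it.

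**A reader might infer that EMSA-SG did lose these patients.** The article does not say so. Its wording is that remote completion may introduce the bias and that such cases would likely have been lost, and it gives no EMSA-SG drop-out figure.

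**A reader might infer that any mixed model must be biased.** That needs loss that depends on the current state beyond earlier scores. It is plausible for loss of mobility, but it is an assumption, and without it the bias is about zero.

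**The size is an upper case.** Remote completion is only offered, and the article expects drop-out in the new cohort too (10%). Partial loss on one side or partial retention on the other shrinks the figure. It is also modest against sampling error: the SD of change is 0.25 × √(2 × 0.4) = 0.224, so with 41 per group (46 less 10%) the standard error is 0.224 × √(2/41) ≈ 0.05.

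**A reader might infer that the comparison as a whole is tilted against the programme.** The documents do not support that. The new cohort must have a life expectancy of at least 24 months and a Charlson index of at most 4, and care is open-label with self-reported EQ-5D. These could favour the programme.

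**The remedy discards outcomes of the sickest patients.** True, and remote completion for other reasons does not reproduce who left EMSA-SG. It therefore belongs beside the all-data estimate, not in its place, and the flag must record the reason. A delta or pattern-mixture analysis would keep all records but needs a guessed parameter.

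**Conclusion.** The point holds in limited form. The cohorts are observed under different rules, the article concedes the likely consequence, and the stated analysis is not adapted to it. Taken alone, this mechanism shrinks the estimated benefit by roughly 0.01 to 0.05 against 0.08. That rests on 15 to 35% being unable to travel, on full loss in EMSA-SG and full retention in the new cohort, and on loss driven by the current state. If earlier scores explain the loss, a mixed model is about unbiased, while a complete-case ANOVA still loses some of the effect.

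A reader might also conclude that only a null result needs caution. With the net direction of all cohort differences unknown, a positive result needs the same care. The analysis should be added because it isolates one component of the difference at little cost, not because the direction of the whole is known.

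**What to change.** In Data analysis:

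1. Flag each EQ-5D record as in-person, remote because disease progression prevented travel, or remote for another reason. Record the reason at the visit, since it is an unblinded judgement.
2. Pre-specify a sensitivity analysis that repeats the primary comparison as a linear mixed model, with the new cohort's records set to missing from the first visit completed remotely because of progression.
3. Report this estimate beside the all-data estimate, with attrition and deaths by cohort and visit.
4. Interpret either a null or a positive primary result in the light of both.

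Cost: one field in the visit record and one more model run. The like-for-like estimate uses fewer observations, has a wider interval, and is slightly conservative when the programme works (0.068 to 0.078 for a true 0.08 in the runs above).
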